### 2.3.3. Objectives

Our **primary objective** is to evaluate the influence of first-author gender on acceptance rates of original articles submitted to leading medical journals that were sent for peer review.

Our **secondary objectives** are: 1) to study the influence of corresponding-author gender and last-author gender on acceptance for publication; 2) to test whether the editor's or associate editor's (see glossary) gender modifies the influence of author gender on acceptance for publication; 3) to determine whether the influence of author gender on acceptance for publication varies over an eight-year period; 4) to determine the proportion of women first authors at each stage of the editorial decision-making process; 5) to possibly explore whether the reasons for manuscript rejection differ between women and men first, last and corresponding authors.

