#### 2.3.7.2. Exposure variables and other confounders

The main exposure factor of interest is **first-author gender**. Other exposure factors assessed are: corresponding and last-author gender, handling-editor gender.

We will also collect data on: year of submission, study design, sample size, statistical significance of main results, funding disclosure, first author’s country of affiliation (reflecting somehow the author’s ethnicity/race), number of authors on the byline, number of reviewers who peer reviewed the manuscript, number (proportion) of women among all reviewers, number (proportion) of reviewers with same region of affiliation as the first author, and first author’s degrees (MD, PhD). If available, we will extract the reasons for rejection mentioned in the journal decision letter.

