#### **2.3.9.2. Statistical analyses**

Statistical analyses will be done by the postdoctorate under the supervision of [name]. We will present descriptive statistics for the proportions of women first authors that were: rejected without external review; sent for external peer review; rejected, accepted or invited to revise a manuscript after external peer review; and rejected and accepted after revision. To take into account clustering at the journal level, we will perform mixed-effects logistic regression to model the influence of the first author's gender on the odds of acceptance for publication, after adjustment for the confounders and covariates (cf. appendix 7) and using the journal as a random effect. We will perform the same logistic regression model to answer our secondary objectives to study the influence of corresponding-author gender or last-author gender on the acceptance for publication. To test whether the handling editor's gender or reviewers' gender modifies the association between first-author gender and the acceptance rate, we will include an interaction term between these two predictors. We will also test interactions of first author gender, respectively with the scope of the journal and with time on a yearly scale. Journals will be anonymised, therefore separate journal effects will not be presented when we publish the results but we will provide journal level data to individual journals upon request.

In the retrospective cohort, we will describe and compare, using Chi-2 tests, the proportion of women first authors for articles at the following points in the decision-making process: rejection without review; sent for peer review; rejected, accepted and sent for revision after peer review; and between articles rejected at any stage versus articles accepted for publication. To test whether the reasons for rejection mentioned in decision letters varies between men and women first (then corresponding and last) authors, we will include an interaction term between these two predictors in a mixed-effects logistic regression model with rejection as the dependent variable and journal as the random factor. All analyses will be performed using STATA 17.0 IC (StataCorp LP, College Station, TX, USA) and R software (version 4.0.5).

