| First author's gender                                        | 0=man, 1=woman                                                                                                                                                                                                                              |
| Corresponding author's gender                                | 0=man, 1=woman                                                                                                                                                                                                                              |
| Study country(ies) of affiliation                            | [...]                                                                                                                                                                                                                                       |
| Number of authors on the byline                              | ##                                                                                                                                                                                                                                          |
| Final decision                                               | 1=immediate rejection, 2=sent for peer-review, 3=rejected after 1 st round of peer-review, 4=rejected after several rounds of peer-review, 5=accepted for publication                                                            |
| Date of final decision                                       | __ / __ / ____                                                                                                                                                                                                                              |
| Study design                                                 | 1=randomised-controlled trial, 2= cohort, prospective, 3=cohort retrospective, 4=cross-sectional, 5=case-control, 6=case reports or case series, 7=systematic review without meta-analysis, 8=systematic review and meta-analysis, 9= other |
| Actual sample size                                           | ####                                                                                                                                                                                                                                        |

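### The reasons-for-rejection model takes rejection as its outcome, so it cannot be estimated and does not answer secondary objective 5

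*Protocol*

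**What the plan says.** Secondary objective 5 (Protocol 2.3.3) is "to possibly explore whether the reasons for manuscript rejection differ between women and men first, last and corresponding authors". Section 2.3.7.2 gives the data source: "If available, we will extract the reasons for rejection mentioned in the journal decision letter".

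The analysis is in the retrospective-cohort paragraph of section 2.3.9.2. Its purpose is "To test whether the reasons for rejection mentioned in decision letters varies between men and women first (then corresponding and last) authors". The two variables, reason and author gender, are both predictors: "we will include an interaction term between these two predictors in a mixed-effects logistic regression model". The outcome and clustering term complete the model: "in a mixed-effects logistic regression model with rejection as the dependent variable and journal as the random factor".

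Nothing in the protocol assigns a reason to accepted papers, limits this model to rejected papers, or makes the reason the outcome. The final-decision field in Appendix 8 codes the stage reached (it begins "1=immediate rejection, 2=sent for peer-review, 3=rejected after 1"), not a reason. Neither Appendix 7 nor Appendix 8 lists a reason-for-rejection variable.

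**The concern.** The model has outcome and predictor the wrong way round. A reason for rejection is recorded because a paper was rejected, so its presence already determines the outcome.

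Objective 5 is about rejected papers only: is the mix of reasons the same for women and men? The model instead sets rejected papers against accepted ones, which have no reasons.

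If reasons are extracted, the analyst must either report output that means nothing or choose another model after seeing the data. The sentence covers first, corresponding and last authors, so three analyses are affected. There is also a risk of misreading, because the failed fit can look like a null result (see the check).

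**Working it through.** The protocol gives no sample size, estimate or power for this analysis, so there is no figure to reproduce. The claim is structural. It was checked by reasoning and then on constructed data.

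**Inputs.** Section 2.3.9.1 gives 3500 accepted and 3500 rejected manuscripts, with 40% women first authors among accepted and 44% among rejected. These are case-control figures, used only as an illustration because no cohort size is stated. Assumed: three reason categories of roughly equal frequency, unrelated to gender. The journal random intercept was left out.

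**Model as written.** With w = 1 for a woman and R_k = 1 for reason k:

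logit P(rejected) = a + b·w + Σ c_k·R_k + Σ d_k·w·R_k

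The protocol does not say how accepted papers are coded, so each possibility is taken in turn.

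1. *Reason missing for accepted papers.* They drop out. All 3500 remaining rows have rejection = 1. The outcome does not vary and no effect can be estimated.

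2. *Accepted papers coded as no reason, and every rejected paper has a reason.* The constructed data are:

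| Reason | Accepted | Rejected |
|---|---|---|
| none | 3500 | 0 |
| 1 | 0 | 1209 |
| 2 | 0 | 1148 |
| 3 | 0 | 1143 |

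This is complete separation. c_k = logit(1) − logit(0), which is infinite. d_k = [logit(1) − logit(1)] − [logit(0) − logit(0)], which is undefined. Fitting the model gave:

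| Maximum iterations | Reason coefficients | SE of interactions | Deviance |
|---|---|---|---|
| 5 | 13.13 | 1.1 | 19.7 |
| 10 | 23.13 | 13.3 to 13.6 | 0.13 |
| 20 | 43.13 | 1981 to 2022 | 6.0 × 10⁻⁶ |
| 30 | 57.13 | 65,600 to 66,948 | 5.5 × 10⁻⁹ |

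The interaction estimates printed as 0.00 at every step. They carry no information: each cell's rejection probability is 0 or 1 whatever the gender mix of the reasons. Sharply different reasons for women and men would give the same picture.

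3. *Some rejected papers also have no recorded reason* (the extraction is conditional on availability). The no-reason group now holds both outcomes, so its logits are finite. Each reason category still has 0 accepted papers. c_k = logit(1) minus a finite value, still infinite, and d_k is still undefined. This is quasi-complete separation.

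A journal random intercept cannot help, because the probability of rejection given a recorded reason is 1 within every journal.

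**What the interaction would mean if it could be estimated.** d_k compares the gender–rejection log odds ratio at reason k with that at the reference category. Equivalently, it is the gender–reason association among rejected papers minus the same association among accepted papers. Objective 5 asks for the first of these terms alone.

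**The model turned round.** Among the 3500 rejected papers, a logistic model for reason 1 (yes/no) on gender fits normally: log odds ratio −0.003, SE 0.072, with no true effect simulated.

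**What it could detect.** Two-proportion comparison, two-sided 5%, 90% power, 44% women, clustering ignored; reason frequencies are assumed. With 3500 rejected papers there are 0.44 × 3500 = 1540 women and 0.56 × 3500 = 1960 men.

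| Rejected papers | Reason frequency in men | Detectable difference (points) | Odds ratio |
|---|---|---|---|
| 3500 | 10% | 3.6 | 1.41 |
| 3500 | 50% | 5.5 | 1.25 |
| 2800 | 10% | 4.0 | 1.47 |
| 2800 | 50% | 6.2 | 1.28 |

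**The case against.** The strongest counter-argument concerns importance. Objective 5 is the last of five, is hedged, and is missing from the aims in the summary (section 1.2). Extraction depends on availability and no reason field is listed, so the analysis may never be run. An analyst would probably notice the failure at the first fit. This is fair, and it limits the priority. It does not rescue the sentence: the hedge covers whether reasons can be obtained, and if they are, the stated model still fails. Nor is this detail left to an SAP, because the protocol fixes the outcome, predictors, interaction and random effect.

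A second objection is that perfect prediction is inferred rather than stated. The protocol records first and last decisions and the number of submissions. If an earlier rejection letter were linked to a paper later accepted, or if rejection meant a stage of rejection, a recorded reason would no longer fix the outcome. The document describes neither arrangement, and the mismatch with objective 5 would remain in both.

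Two practical objections stand. The change needs more than a new sentence, because a variable and its categories must be defined. The sentence also names no covariates, so any adjustment set has to be written out.

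**Conclusion.** The concern holds. As written, the interaction between author gender and reason for rejection is not estimable under any coding consistent with the protocol, and more data would not change that. If it could be estimated, it would still address a different question from objective 5.

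The conclusion rests on reasons being recorded only for rejected papers, which is the plain meaning of section 2.3.7.2. The 3500/3500 split and the three categories serve only as illustration; the result does not depend on them.

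The effect is confined to one exploratory secondary objective, for all three author positions. The primary model, the other secondary models and the chi-squared comparisons are untouched. It should be corrected before any reasons are analysed.

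**What to change.** Replace the sentence in section 2.3.9.2 with an analysis that:

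- is restricted to rejected manuscripts with an extracted reason, stating which rejection codes in Appendix 8 count;
- takes the reason as the dependent variable: one mixed-effects logistic model per reason category if a paper can have several, or a multinomial model if one main reason is assigned;
- uses first-author gender as predictor and journal as random effect, repeated for corresponding and last authors;
- names any covariates and limits them to those fixed at submission, such as year of submission, study design and sample size. Appendix 7 items that arise during review, such as number of revisions and number of reviewers, should stay out.

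Add a reason-for-rejection variable with defined categories to the data list, and report how many rejected papers have a reason available, by author gender.

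The cost is one rewritten sentence, one new field and its coding rules. The planned decision-letter extraction and the software stay the same, and no additional manuscripts are needed.

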#### **2.3.10. Ethical considerations**

As the project will not involve human participants but data routinely collected from articles submitted for publication in various medical journals, we do not expect any major ethical issues. However, to guarantee the anonymity of the authors, reviewers, and editors, we will remove personal identifying variables from the final database, all names of individuals will be removed and only their gender included. We will also preserve journal anonymity by presenting results without naming the journals; journals will be identified by a coded variable. The protocol was submitted to the Geneva Cantonal Ethics Commission on March 23, 2019. It was exempted from ethical approval on April 24, 2019 but received full support (appendix 1). Personal data will be provided by journals under confidentiality agreements or research contracts.

## THE ATHENA STUDY: FIRST AUTHOR'S GENDER AND ACCEPTANCE FOR PUBLICATION

## 2.4. Schedule and milestones

### 2.4.1. Timeframe

| Tasks ( person in charge )                                                                                                 | 2021 |   |   |   |   |   |   |   |   |    |    |    | 2022 |   |   |   |   |   |   |   |   |    |    |    |
|-----------------------------------------------------------------------------------------------------------------------------------|------|---|---|---|---|---|---|---|---|----|----|----|------|---|---|---|---|---|---|---|---|----|----|----|
|                                                                                                                                   | 1    | 2 | 3 | 4 | 5 | 6 | 7 | 8 | 9 | 10 | 11 | 12 | 1    | 2 | 3 | 4 | 5 | 6 | 7 | 8 | 9 | 10 | 11 | 12 |
| Confidentiality agreement procedure from journals                                                                                 |      |   |   |   |   |   |   |   |   |    |    |    |      |   |   |   |   |   |   |   |   |    |    |    |
| Procedure for gender determination                                                                                                |      |   |   |   |   |   |   |   |   |    |    |    |      |   |   |   |   |   |   |   |   |    |    |    |
| Exploration of available data in the BMJ database ( postDoc )                                                              |      |   |   |   |   |   |   |   |   |    |    |    |      |   |   |   |   |   |   |   |   |    |    |    |
| Journals recruitment ( main applicant and postdoc )                                                                        |      |   |   |   |   |   |   |   |   |    |    |    |      |   |   |   |   |   |   |   |   |    |    |    |
| Creation of algorithms for automatic data extraction in pdfs ( Swiss Institute of Bioinformatics, SIB )                    |      |   |   |   |   |   |   |   |   |    |    |    |      |   |   |   |   |   |   |   |   |    |    |    |
| Data acquisition for the case-control study in the pdfs ( SIB )                                                            |      |   |   |   |   |   |   |   |   |    |    |    |      |   |   |   |   |   |   |   |   |    |    |    |
| Data acquisition for the case-control study in the journal databases ( journal editors, main applicant and postDoc )       |      |   |   |   |   |   |   |   |   |    |    |    |      |   |   |   |   |   |   |   |   |    |    |    |
| Collection of information on the editorial decision-making process at each participating journal ( main and co-applicant ) |      |   |   |   |   |   |   |   |   |    |    |    |      |   |   |   |   |   |   |   |   |    |    |    |
| Collection of data for retrospective cohort study ( postDoc )                                                              |      |   |   |   |   |   |   |   |   |    |    |    |      |   |   |   |   |   |   |   |   |    |    |    |
| Data analysis and interpretation of the case-control study ( postDoc, main applicant )                                     |      |   |   |   |   |   |   |   |   |    |    |    |      |   |   |   |   |   |   |   |   |    |    |    |
| Writing of main manuscript (case-control study), conferences ( postDoc, main/co applicants, partners )                     |      |   |   |   |   |   |   |   |   |    |    |    |      |   |   |   |   |   |   |   |   |    |    |    |

[figure not shown]

THE ATHENA STUDY: FIRST AUTHOR'S GENDER AND ACCEPTANCE FOR PUBLICATION

| Tasks ( person in charge )                                                                                                    | 2023 |   |   |   |   |   |
|--------------------------------------------------------------------------------------------------------------------------------------|------|---|---|---|---|---|
|                                                                                                                                      | 1    | 2 | 3 | 4 | 5 | 6 |
| Writing/critical revision of main manuscript (case-control study) ( postDoc, main/co applicants, partners )                   |      |   |   |   |   |   |
| Dissemination of study results findings ( main/co-applicants, postDoc )                                                       |      |   |   |   |   |   |
| Data analysis and interpretation of secondary study ( postDoc, main/co applicants )                                           |      |   |   |   |   |   |
| Writing/critical revision of secondary manuscript (case-control study), conferences ( postDoc, main/co applicants, partners ) |      |   |   |   |   |   |
| Dissemination of second study results findings ( main/co-applicants, postDoc )                                                |      |   |   |   |   |   |

## 2.5. Relevance and impact

### 2.5.1. Scientific relevance

Before it can reach publication, an original article is left in the hands of individuals in the editorial team who could, as in society, apply their own rules and possibly gender discrimination, whether consciously or not. All submitted manuscripts go through a preliminary editorial screening during which assessments are made as to whether the topic is within the journal's scope, author instructions were respected, and general quality standards are met; it is then sent out for peer review; once the required number of reviews is received, the editor(s) consider the experts' opinions and make an initial decision to accept, reject or request revision, or take it to a committee and/or statistical reviewer for further assessment. Revised papers are re-evaluated by the original handling editor, who either makes a decision (or refers it back to a committee that may include a statistical advisor) or sends the manuscript for further peer review prior to making a decision. Editors may request multiple manuscript revisions. This editorial decision-making process may vary in the assessment criteria used, depending on the journals; the final decision could be left to a single individual (the handling editor) or to a group of persons (Figure 2). The BMJ, one of the largest participating journals, includes patient and public reviewers in the review process (Figure 3).

This research will provide important insights into the mechanism of gender bias in medical research. We will specifically explore whether gender might interfere with chances of article publication. We are looking for additional reasons to explain significant differences in the scientific productivity (lower number of publications and smaller h-index in women compared to men) between women and men researchers. Gender might not be the only factor inducing bias in the assessment of research productivity; we would need to acknowledge intersectionality, especially with regards to race and ethnicity of the authors, and the risk of additional and compounded bias. For example, an editor/reviewer could vaguely assume someone's race or ethnicity based on their first name, and conscious/unconscious bias could affect their decision making on top of gender bias. It is less likely that other aspects of diversity, e.g. age or sexual orientation, could creep into the editorial and peer review process as it is almost impossible to guess these personal characteristics based on the first name of a person without knowing them. This could potentially be a limitation as up until now, journals do not collect or report on the race/ethnicity of authors. However, we will use a proxy by describing the authors' country of affiliation. Research results will be published in an open-access journal and presented at a gender-centred conference (e.g., Women in Science and Healthcare symposium, Women in STEM conference).

**Figure 2.** Editorial decision-making process.

[figure not shown]

**Figure 3.** Editorial & review decision-making process at the BMJ Group.

[figure not shown]

